*Note*. Sessions can be repeated with families who choose to continue coaching over a longer period of time (responsive coaching condition only)

The *secondary TBRI intervention* is provided after completion of the primary intervention and includes in-home support following discharge. Youth and caregivers randomly assigned to Coaching receive either Structured (4 TBRI In-Home Trainings) or Responsive Coaching (2+ TBRI In-Home Trainings with additional trainings as requested by the family or triggered by SU or risk factors observed/identified by research staff).

For the purpose of this project, TBRI intervention components are delivered by 1–2 Research Assistants (RAs) who are also trained as TBRI Practitioners. All TBRI Practitioners have a minimum Bachelor’s Degree in human services areas, more than 2 years of clinical experience and fieldwork in high-risk juvenile and adult populations, receive a minimum of 20-h onboard training and skills development as well as ongoing training/supervision. All caregiver sessions are delivered virtually to enable caregivers who do not live close to the site where their youth resides. Sessions are synchronous, and participants are provided an “orientation” to the online platform prior to the first session. Youth sessions are delivered in person at the facility by RAs, with support from non-correctional staff (e.g., clinical staff). Nurture groups are delivered in a group format with youth joining virtually as a group from the facility and caregivers joining individually from their homes. Sites determine when and where youth sessions will be delivered, including which staff to involve (i.e., therapeutic staff who could participate in intervention activities. Staff are provided training on logistics and strategies to address potential behavioral issues and support a youth in need.

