### Hybrid design: effectiveness trial

The effectiveness trial includes a comparison of youth enrolled in SRP to youth enrolled in SRP plus TBRI, whereby each facility serves as its own control. Because caregivers may need support after their youths’ release, three versions of TBRI are compared, with youth in the SRP + TBRI cohort being randomly assigned to one of three support formats: (1) TBRI Training only (no in-home TBRI support), (2) TBRI Training + Structured Coaching (4 sessions), and (3) TBRI Training + Responsive Coaching (2+ sessions, triggered by youth need/risk).

The effectiveness trial proceeds in 3 stages: Standard Reentry Practice (SRP) only (baseline control), SRP + TBRI, and Facility Sustainment (see Fig. 2). **Stage 1 - SRP**: sites engage in standard practice; study activities include youth and caregiver assessments over 18 months. Each site serves as its own control. A total of 120 youth/adult dyads are recruited across the nine sites. The length of SRP varies between 8 months (Wave 1) and 12 months (Wave 3). **Stage 2 - SRP + TBRI Intervention:** sites continue to engage in standard practice; TBRI intervention is delivered to youth and caregivers enrolled in the study; youth and caregiver assessments are conducted over an 18-month period. A total of 240 youth/adult dyads are recruited across the nine sites. **Stage 3 - Facility Sustainment**: youth/caregiver recruitment, baseline assessment, and interventions cease; youth and caregiver follow-up interviews continue; responsibility for implementing primary and secondary TBRI intervention components is transferred to the JJ facility.

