**Fig. 2 Fig2:**
[figure not shown]
Recruitment and data collection timeline

At the participant level (see Fig. 3), for both SRP and SRP + TBRI stages, youth and safe adults are recruited/consented 2–3 months prior to discharge, and individually complete baseline at recruitment and follow-up interviews at 3- (within 2 weeks of discharge), 6-, 12-, and 18-months post-baseline. For dyads recruited during the Stage 2 – SRP + TBRI Intervention period, the primary TBRI intervention sessions begin after baseline assessment while the youth are in the residential facility. At the point of discharge, dyads are randomly assigned to one of 3 TBRI in-home support conditions, with probabilities equal to 1:3 within each site. This overall design enables comparison of TBRI versus SRP plus a randomized control trial comparing TBRI support conditions.

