### Measurement and outcomes

For the effectiveness trial, data come from 3 sources: (1) youth self-report at Months 0, 3, 6, 12, and 18; monthly post-release check-ins, (2) JJ facility records (e.g., recidivism, treatment utilization), and (3) caregiver self-report with a timeframe identical to youth. Table 4 depicts research goals, assessment instruments, data collection timeline, and youth and/or caregiver single or dyadic perspective on each construct. The primary outcome is *days to youth initiation* of non-medical opioid use: measured by (a) Timeline Followback [51], (b) TCU Drug Screen 5 with Opioid Supplement (TCU DS 5-OS) [52], and (c) Substance Use Involvement items from the HEAL Prevention Cooperative [53]. Secondary outcomes include putative change mechanisms, public health, and public safety outcomes. Putative change mechanisms include youth self-regulation and self-efficacy (e.g., “How confident are you that you will not misuse a prescription opioid in the next 30 days”) [53] and youth/caregiver psychosocial functioning and relationships between youth and caregivers. Self-regulation is measured with the TCU Adolescent Thinking forms on regulation (TCU THK-NUY, TCU THK-PUY; decisions influenced by positive or negative emotion) [54], supplemented with the delayed discounting task (DD task) [55], Difficulties in Emotion Regulation Scale (DERS) [56], and Barkley Deficits in Executive Functioning Scale-CA Short Form (BDEFS-CA) [57]. *Psychosocial functioning* is measured by the Strengths and Difficulties Questionnaire for youth (SDQ) [58], Generalized Anxiety Disorder Assessment (GAD-7) [59], Patient Health Questionnaire (PHQ-8) [60], PROMIS-Pain [61], and items that evaluate youth’s self-reported efficacy to resist opioids (“How confident are you that you will not misuse a prescription opioid in the next 30 days?”) [53]. *Youth/caregiver relationships* are measured using the Family Assessment Device (FAD) [62], the Experiences in Close Relationships – Relationship Structures (ECR-RS) [63], and the Attachment, Relational Frustration, and Discipline Practices scales from the Behavior Assessment System for Children Parent Relational Questionnaire (BASC-3) [64].

**Table 4 Tab4:** An overview of assessment and timeline for the effectiveness of TBRI intervention

Construct and Instrument	Measurement Time Points						Participant	
	Baseline	MO 3	MO 6	MO 12	MO 18	Monthly check-in	Youth	Caregiver
Youth SU								
TLFB		x	x	x	x		x	

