#### Power

For H1 examining the effectiveness of SRP + TBRI compared to SRP alone, the proposed Intent to Treat (ITT) sample will include 360 youth/safe adult dyads (120 SRP, 240 TBRI), with 80 randomized to each TBRI condition. SAS PROC POWER for rank tests comparing 2 survival curves found that, if overall opioid initiation rates are 35% (SRP) vs. 25% (all TBRI groups) at any assessed time point, power is estimated to be at 93% (*α* = .05). For H2 comparing the 3 TBRI conditions, SAS PROC POWER for rank tests comparing 2 survival curves found that for sample sizes of 80 in each group, power = .80 when the hazard ratio = 1.57. When the combined TBRI groups are tested against SRP, power = .80 when the hazard ratio = 1.37.

For H3 and H4 pertinent to the organizational TBRI intervention, the expected sample (nine sites, up to 90 staff participants per site) and the response rate of 25% gives an expected sample of 203 participants. A small effect size (0.20), a power of 0.80, significance level of 0.05, and an intraclass correlation of 0.10 are used to calculate the minimum required sample size. Repeated measures design comparing staff participants over time results in a minimum sample size of 43 participants. To be more conservative, the same parameters are used for a mixed-effect design (four repeated measures by nine sites), yielding a minimum sample size of 189 participants.

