### Data analysis plan

For all analyses, an ITT approach is used, where all study participants are included in analyses. For H1 and H2, comparisons of survival curves for each group are performed using SAS PROC PHREG and PROC GLIMMIX using the log rank test with the Sidak multiple-comparison adjustment, with the primary outcome as the dependent variable. Differences between groups on secondary outcomes and change over time in implementation measures (e.g., TBRI use) are examined using repeated measures ANOVAs (SAS 9.4, PROC MIXED), with study site as random effects and condition, time, and interactions as fixed factors. Because SU rates are generally lower among JJ females, sex as a biological variable is examined as a moderator of differences in outcomes using univariate analyses (e.g., chi square, t-tests, ANOVA); when significant, tests of moderation are undertaken as part of all analyses. Putative change mechanisms are investigated as mediators of the Group – Primary Outcome relationship and structural equation modeling (SEM; using Mplus) is used to examine sex differences in mediation. For H3, changes in the outcomes over time are examined using repeated measures ANOVAs (SAS 9.4, PROC MIXED), with study site as random effects and time and time × site interactions as fixed factors. For H1–3, a log rank test is used to assess study dropout; stochastic multiple-imputation provides maximum likelihood estimates, accounts for uncertainty in missing values, and provides unbiased estimates of the treatment effect if data are missing at random.

Qualitative data from focus groups are transcribed and qualitatively coded (in Atlas.ti) by at least 2 research staff. An iterative process of coding and thematic analysis [84] are used to understand routine practices employed, nuances in the use of trauma-informed and child-centered strategies, facility facilitators/barriers to uptake of new interventions, general penetration of TBRI within the facility, and facility interest in sustaining and/or expanding TBRI practices.

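### For the coaching comparison, the stated repeated measures model on its natural reading counts Months 0 and 3 as outcome levels and names neither a baseline covariate nor a post-randomisation contrast, which costs power on secondary outcomes

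*Protocol article*

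**What the plan says.** All references are to the protocol article.

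- **Model (Data analysis plan).** "Differences between groups on secondary outcomes and change over time in implementation measures (e.g., TBRI use) are examined using repeated measures ANOVAs", fitted in PROC MIXED "with study site as random effects and condition, time, and interactions as fixed factors". The covariates described under Measurement and outcomes are background, family and service variables. The baseline score of the outcome itself is not among them.
- **Visits (Measurement and outcomes, Table 4).** The article lists "youth self-report at Months 0, 3, 6, 12, and 18". Table 4 shows Baseline and MO 3 as columns beside MO 6, 12 and 18.
- **Assignment (Hybrid design: effectiveness trial).** "At the point of discharge, dyads are randomly assigned to one of 3 TBRI in-home support conditions". Recruitment and baseline come 2 to 3 months before discharge. The later visits are "follow-up interviews at 3- (within 2 weeks of discharge), 6-, 12-, and 18-months post-baseline".
- **Coaching (Trust-based Relational Intervention, text after Table 3).** The secondary intervention "includes in-home support following discharge".
- **Size (Power).** The TBRI cohort is 240 dyads, "with 80 randomized to each TBRI condition".
- **DERS (note to Table 4).** The trait version is used at baseline and the state version at every follow-up.

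**The concern.** A single model is written for all secondary group comparisons, but the groups separate at different times. In TBRI versus SRP, the primary intervention is given before discharge, so Month 3 is a true outcome visit. In the coaching comparison the arms separate only at discharge. Month 0 cannot show a coaching effect, and Month 3 can show little.

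If those visits are ordinary levels of time, the condition term averages the coaching effect with visits where it is absent. The condition-by-time term does pick up the divergence, but spreads it over many degrees of freedom. The scores taken before coaching are most useful as covariates, and the model does not use them that way.

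At stake are the outcomes of Aim 1(b) and 1(c), which also supply the candidate mediators. A real coaching effect on self-regulation or psychosocial functioning could be reported as no difference between formats, although the data were able to show it.

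**Working it through.** The article gives no power, effect size, SD or within-person correlation for secondary outcomes, so there is no stated figure to reproduce.

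**Dilution and degrees of freedom, from Table 4.** Dilution = (visits at Months 0 and 3) / (all visits). Interaction df = (3 - 1) x (visits - 1).

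| Instruments | Visits (months) | Dilution | df |
|---|---|---|---|
| DERS, GAD-7, PHQ-8, PROMIS Pain | 0, 3, 6, 12, 18 | 2/5 = 40% | 8 |
| Self-efficacy; ECR-RS; FAD Affective Responsiveness | four, including 0 and 3 | 2/4 = 50% | 6 |
| TCU THK, BDEFS-CA, BASC-3; SDQ; other FAD scales | 0, 6 and 12 or 18 | 1/3 = 33% | 4 |
| DD task | 0, 3, 12 | 2/3 = 67% | 4 |

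If SRP were a fourth condition in the same model, the five-visit interaction would have 3 x 4 = 12 df.

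**Power for a five-visit instrument.** From the article: 80 per arm, three arms. Assumed: SD 1, equal correlation rho between visits, complete data, effect 0 at Months 0 and 3, and d = 0.3 in both coaching arms at Months 6, 12 and 18. Arm effects 0, 0.3, 0.3 have mean 0.2 and squared deviations 0.04 + 0.01 + 0.01 = 0.06, so the base quantity is 80 x 0.06 = 4.8. Power comes from the noncentral F at alpha 0.05. At rho = 0.5 the noncentralities are:

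1. Condition, mean of five visits: effect factor 3/5, variance (1 + 4 rho)/5 = 0.60. 4.8 x 0.36 / 0.60 = 2.88 on 2 df.
2. Condition by time: the visit pattern (0, 0, 1, 1, 1) has sum of squares 1.2 about its mean. 4.8 x 1.2 / (1 - 0.5) = 11.52 on 8 df.
3. Mean of Months 6-18 minus mean of Months 0 and 3: variance (1 - rho)(1/3 + 1/2) = 0.417. 4.8 / 0.417 = 11.52 on 2 df.
4. Mean of Months 6-18 adjusted for Month 0: variance (1 + 2 rho)/3 - rho² = 0.417. Again 11.52 on 2 df.
5. Mean of Months 6-18 adjusted for Months 0 and 3: variance (1 + 2 rho)/3 - 2 rho²/(1 + rho) = 0.333. 4.8 / 0.333 = 14.4 on 2 df.

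| Test | rho 0.4 | rho 0.5 | rho 0.6 |
|---|---|---|---|
| 1. Condition | 35% | 31% | 27% |
| 2. Condition by time | 56% | 66% | 78% |
| 3. Focused post-minus-pre contrast | 79% | 86% | 93% |
| 4. Adjusted for Month 0 | 84% | 86% | 90% |
| 5. Adjusted for Months 0 and 3 | 90% | 93% | 96% |

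Lines 2 and 3 have the same noncentrality. The gap between them is the price of 8 df instead of 2.

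**If Month 3 cannot count as a pre-coaching visit.** The contrast of Months 6-18 minus Month 0 alone has variance 0.667 + 1 - 2 x 0.5 = 0.667 at rho = 0.5. The noncentrality is 4.8 / 0.667 = 7.2, and power is 66% against 86% with Month 0 as covariate.

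**Other cases.** For TCU THK (0, 6, 12) at rho = 0.5, power is 34% (condition), 49% (interaction) and 79% (adjusted for Month 0). For the DD task, the condition term has about 11%. With an effect that fades (0.45, 0.30, 0.15) and rho 0.4 to 0.6, the interaction reaches 75-92% and the contrast adjusted for Months 0 and 3 reaches 90-96%. With a graded effect (0, d/2, d), d = 0.4 and rho = 0.5, the condition term has 40%, the interaction 81%, the focused contrast 95% and the contrast adjusted for both visits 98%.

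**The case against.** The strongest reply is that the article does not force the loss. It names the model's factors but not the term or contrast that carries the comparison. The same model allows a focused contrast (line 3), which already reaches about 86-87% at rho = 0.5. Such a choice is commonly left to a full analysis plan, which is not shown. This stands as a limit on the size of the point: measured against that contrast, the covariate model gains nothing at rho = 0.5 with Month 0 alone and about 7 points with both visits. It does not remove the point. The article states a method that names no baseline-score covariate, and the focused contrast reaches that power only if Month 3 is treated as a pre-coaching visit.

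Four stronger readings are tempting and not supported:

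- *That every secondary outcome loses 40% or is tested on 8 df.* Those figures fit only the five-visit instruments. Every relationship measure has three or four visits.
- *That neither planned test uses the pre-randomisation scores.* The interaction does, by differencing within person, which is why its power rises with rho. It spreads the information over too many df.
- *That Month 3 precedes assignment and coaching.* The article puts it within 2 weeks of discharge without saying on which side. Some interviews may follow assignment and a first session, so unconditional adjustment for Month 3 could remove part of an early effect.
- *That Month 0 should simply be dropped from TBRI versus SRP.* That comparison is sequential and not randomised, so removing Month 0 without adjusting for it would leave cohort differences uncorrected.

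**Conclusion.** The point holds as one of efficiency, for the coaching comparison only. A repeated measures ANOVA is a valid analysis here. No bias or inflation of type I error in this randomised comparison is shown, although a reader might infer one.

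On the natural reading of the stated factors, the available tests are a diluted condition term or an omnibus interaction, with about 31% or 66% power in the main example. A baseline-adjusted or focused comparison of post-randomisation visits has about 86-87%, and about 93% if Month 3 is also a legitimate covariate. Treating Months 0 and 3 as time levels is inferred from Table 4 and not stated in the Data analysis plan. The power figures rest on assumed values for effect size, correlation and pattern over time. Their ordering (condition below interaction below the contrast adjusted for Months 0 and 3) held in the cases shown. DERS adds a separate reason: its Month 0 score comes from a different version, so it is not a comparable outcome level.

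The change is worth making, because it raises precision with data already planned and costs almost nothing.

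**What to change.** In the Data analysis plan, separate the two comparisons.

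- **Three support formats (randomised).** Fit PROC MIXED to the post-randomisation visits (Months 6, 12 and 18, as collected for each instrument), with site as now and the Month 0 score as covariate. Add the Month 3 score only where it was collected before assignment and before any coaching. The main test is the condition effect averaged over these visits. Condition by time is secondary.
- **DERS.** Use the Month 0 trait score only as a covariate, never as a level of the outcome.
- **TBRI versus SRP (not randomised).** Keep an adjustment for Month 0, as covariate or as change from baseline, and treat Month 3 as an outcome visit.

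This costs a few sentences of analysis wording and no new data, apart from checking the date of each Month 3 interview against assignment and first coaching session. The downside is that an effect that reverses sign between visits would show only in the secondary interaction test.

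### Sex moderation is tested only after a significant univariate result for sex; as worded, that screen tests a main effect and can miss real effect modification

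*Protocol article*

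**What the plan says.** The rule stands in one sentence of the Data analysis plan in the protocol article. Its reason is a difference in level: "Because SU rates are generally lower among JJ females". It then names the tests and the condition: "sex as a biological variable is examined as a moderator of differences in outcomes using univariate analyses (e.g., chi square, t-tests, ANOVA); when significant". Moderation testing is thus a second step, reached only if the first step is significant.

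The next sentence adds a sex analysis with no condition attached: "structural equation modeling (SEM; using Mplus) is used to examine sex differences in mediation". The section states no unconditional test of condition by sex on any outcome.

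The primary outcome is days to first non-medical opioid use (Measurement and outcomes), compared by survival methods for H1 and H2. The Power section plans "360 youth/safe adult dyads (120 SRP, 240 TBRI), with 80 randomized to each TBRI condition" and reasons from overall rates: "if overall opioid initiation rates are 35% (SRP) vs. 25% (all TBRI groups) at any assessed time point". It gives no rates by sex, and the article does not state the expected share of girls.

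**The concern.** Moderation by sex means that the TBRI effect differs between boys and girls, which is a condition-by-sex interaction. A chi-square or t-test of outcome by sex asks whether boys and girls differ on average over conditions. The two questions are separate:

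- The interaction can be large while the overall rates by sex coincide. The screen then stays closed and the interaction is never examined.
- The overall rates can differ, as the plan itself expects, while TBRI works equally well in both sexes. The screen then opens for a reason that has nothing to do with TBRI.

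The named tests also take no account of censoring, so for days to initiation the screening step does not match the time-to-event outcome.

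At stake is whether a benefit confined to one sex, or an adverse effect in one sex, would be reported, and whether the set of outcomes given an interaction test is fixed in advance or picked by the data.

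**Working it through.** The article gives no figure for this analysis, so there is none to reproduce. The check compares the screened rule with a direct interaction test.

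**Inputs from the article.** 120 SRP and 240 TBRI youth; α = 0.05 (Power).

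**Assumptions.** Two-sided tests; 20%, 30% or 50% girls, the same share in both conditions; sex-specific initiation rates as listed; initiation treated as yes/no for simplicity.

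**Overall rate by sex.** With a 1:2 allocation it is (SRP rate + 2 × TBRI rate) / 3.

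- A, reversal with equal overall rates: boys (35 + 2×20)/3 = 25%; girls (15 + 2×30)/3 = 25%.
- B, benefit in boys only, equal overall rates: boys 25% as in A; girls (25 + 2×25)/3 = 25%.
- C, reversal from a common SRP rate: boys (30 + 2×15)/3 = 20%; girls (30 + 2×45)/3 = 40%.
- D, no interaction (same odds ratio in both sexes): boys 40% to 29.0%, overall (40 + 2×29.0)/3 = 32.7%; girls 20% to 13.3%, overall (20 + 2×13.3)/3 = 15.5%.

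**Tests.** Screen: two-proportion (chi-square) test of initiation by sex. Direct: Wald test of the difference between boys and girls in the log odds ratio for TBRI, with variance Σ 1/[n p(1−p)] over the four sex-by-condition cells. Screened rule: both significant.

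**Hand check with 30% girls** (cells of 84 and 168 boys, 36 and 72 girls).

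- A: log odds ratios are −0.767 (boys) and +0.887 (girls), difference −1.655. Variance = 1/19.11 + 1/26.88 + 1/4.59 + 1/15.12 = 0.374, so SE = 0.611, z = 2.71, and power ≈ Φ(2.71 − 1.96) = 77%.
- B: difference −0.767. Variance = 1/19.11 + 1/26.88 + 1/6.75 + 1/13.5 = 0.312, so SE = 0.558, z = 1.37, and power ≈ Φ(1.37 − 1.96) = 28%.

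**Simulation** (at least 200,000 trials per cell; 0.5 added to each count for the Wald test). Results for 20% / 30% / 50% girls:

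| Scenario | Screen opens | Direct test significant | Both (screened rule) |
|---|---|---|---|
| A: boys 35→20, girls 15→30 | 5 / 5 / 5% | 66 / 80 / 88% | 3 / 4 / 4% |
| B: boys 35→20, girls 25→25 | 5 / 5 / 5% | 20 / 27 / 32% | 1 / 1 / 2% |
| C: boys 30→15, girls 30→45 | 93 / 97 / 99% | 72 / 82 / 86% | 68 / 80 / 85% |
| D: no interaction | 86 / 94 / 97% | 3 / 4 / 5% | 3 / 4 / 5% |

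The hand values for A and B agree with the simulated 80% and 27%. In A and B the screen opens only at its own type I error rate. In D it opens almost always although there is nothing to find. In C it opens because the reversal itself produces a gap of 20% against 40%, and little is lost.

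**The case against.** **Wording.** The sentence speaks of sex as a moderator, the list of tests is only by example, and an ANOVA could hold a condition-by-sex term. In a condensed article, the first step might already be meant as an interaction test. This earns the qualifier *as worded*, but no more. A t-test cannot hold an interaction, a chi-square of outcome by sex does not test one, the stated reason is about level, and a separate later step called "when significant, tests of moderation are undertaken as part of all analyses" would be redundant if the first step had already tested moderation.

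**Size.** A reader might infer that the rule would miss any real reversal. The figures do not support that: scenario C keeps nearly all its power. Scenario A is a worst case, with TBRI doubling initiation in girls and overall rates exactly equal, whereas the plan expects lower use in females. At 50% girls it also implies no overall effect (25% in both conditions), unlike the planning rates of 35% and 25%. For the more ordinary scenario B there is much less power to lose. If boys go from 40% to 27% and girls stay at 20%, closer to the plan's expectation, the screen opens in 48–70% of trials and the direct test is significant in only 11–20%. These limits stand.

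**Censoring.** Once the screen is passed, moderation is tested within all analyses, including the survival models. The censoring point therefore applies to the screening step alone.

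**Weight.** None of H1 to H4 concerns sex, and the mediation analysis by sex carries no condition. Both are true. The mediation analysis examines pathways, however, and does not replace a test of whether the TBRI effect on the outcome differs by sex.

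**Conclusion.** The concern holds as a *can miss*. As worded, the plan makes tests of sex moderation conditional on a main effect of sex, which does not measure effect modification. The loss runs from near total when the overall rates by sex coincide (screen open in about 5%, against direct power of 66–88% for a reversal and 20–32% for benefit in boys only) to small when the reversal creates a sex difference (68–85% against 72–86%). With no interaction but lower rates in girls, the screen opens in 86–97%. All of this rests on assumed sex-specific rates, an assumed 20–50% girls and a yes/no outcome.

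A reader might also infer that the main comparisons are compromised. They are not: this is a subsidiary analysis, and the rule does not alter the H1 or H2 estimate. Nor would removing the screen make the trial well powered for sex moderation of ordinary size.

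**What to change.** Delete the univariate condition. Fit the condition-by-sex interaction directly in the Cox model for days to initiation and in the mixed models for key secondary outcomes. Report sex-specific effects with confidence intervals whatever the main effect of sex. Label these analyses exploratory and say that power for ordinary sex moderation is low.

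Give the right reason for sex in each model. Under Randomization and Overall study design, the urn works only among the three TBRI support formats, so balancing justifies sex as a term for H2. SRP against TBRI (H1) compares successive, non-randomised cohorts, and there sex belongs as a prognostic covariate.

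The cost is one rewritten sentence and one model term, with no new data. The downside is a few extra interaction tests with low power.

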## Methods/design

### Research aims

The specific aims of the LeSA Project are to: (1) test the effectiveness of the TBRI intervention and its different support formats – no in-home TBRI support, Structured Coaching, Responsive Coaching – on (a) preventing initiation and/or escalation of opioid use, (b) public health and public safety outcomes, (c) putative change mechanisms, including self-regulation, psychosocial functioning, and relationship with a safe adult; (2) document factors related to TBRI implementation and sustainment; and (3) estimate the start-up and implementation costs and cost-effectiveness of TBRI support options relative to standard re-entry practices in achieving lower rates of opioid initiation and reductions in healthcare and JJ system costs.

Primary hypotheses are as follows:
H1: Compared to youth receiving Standard Re-entry Practices (SRP) only, youth receiving TBRI in addition to SRP are less likely to initiate opioid use following discharge.H2: Compared to no in-home TBRI support, youth receiving Structured or Responsive Coaching are less likely to initiate opioid use following discharge, with the longest time to initiation occurring among youth receiving Responsive Coaching.H3: TBRI is most effective for preventing opioid initiation when facilities routinely use TBRI strategies within their residential settings, given increases in continuity as the youth transitions home from residential care.H4: The cost of implementing TBRI + SRP is higher than SRP alone, with higher cost-effectiveness when TBRI is added.

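### The model fixed for H3 has no condition term and no facility TBRI-use term, so it cannot test H3, and the power figure labelled H3 and H4 bears on staff measures only

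*Protocol article*

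**What the plan says.** Research aims lists H3 among the primary hypotheses: "TBRI is most effective for preventing opioid initiation when facilities routinely use TBRI strategies within their residential settings". The section on the implementation overlay repeats the purpose: staff survey data are to show how facility-level trauma-informed care moderates the effectiveness of the primary and secondary intervention.

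The Data analysis plan assigns the methods as follows.
- **H1 and H2:** "For H1 and H2, comparisons of survival curves for each group are performed using SAS PROC PHREG and PROC GLIMMIX", with the primary outcome as dependent variable.
- **Secondary outcomes and implementation measures:** repeated measures ANOVAs "with study site as random effects and condition, time, and interactions as fixed factors".
- **H3:** "For H3, changes in the outcomes over time are examined using repeated measures ANOVAs (SAS 9.4, PROC MIXED), with study site as random effects". The fixed part of this model is limited to time and its interaction with site.

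The Power section states its basis for the last two hypotheses: "For H3 and H4 pertinent to the organizational TBRI intervention, the expected sample (nine sites, up to 90 staff participants per site". It expects 203 staff at a 25% response. With an effect size of 0.20, power 0.80, significance level 0.05 and intraclass correlation 0.10, it derives minimums of 43 staff (repeated measures) and 189 staff (four measures by nine sites).

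The Discussion adds that multilevel modelling can be used to examine the added value of TBRI by how far sites use TBRI.

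**The concern.** Testing H3 needs three things: a youth opioid-initiation outcome, a contrast between TBRI and standard re-entry practice, and a measure of facility TBRI use that is allowed to modify that contrast. The H3 sentence supplies neither the contrast nor the modifier, and it leaves the outcome unnamed. If it is followed as written, a result will be reported under a declared primary hypothesis on which it does not bear.

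The power statement adds to the problem. A reader who sees 203 expected against a minimum of 189 will conclude that H3 and H4 are adequately sized. H3 has its outcome in youth and its modifier varies over only nine facilities. H4 concerns cost and cost-effectiveness. The number of staff who answer a survey determines power for neither.

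**Working it through.** **1. Terms that H3 needs, against terms in the H3 sentence**
- Outcome: H3 needs opioid initiation. The sentence says only that outcomes change over time. Measurement and outcomes defines the primary outcome as days to initiation, one possibly censored time per youth, which a repeated measures ANOVA over time does not analyse.
- Condition: needed, not listed. The sentence for secondary and implementation outcomes does list it, so the protocol names condition where it wants it.
- Facility TBRI use: needed, not listed.
- Condition by facility use: needed, not listed. Time by site can show that sites change differently. It cannot show that they differ according to TBRI use.
- Site is declared random while time by site is declared fixed, which leaves the model itself unclear.

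**2. The plan's own power figures**
- Expected staff: 9 × 90 = 810, and 810 × 0.25 = 202.5, so 203 reproduces.
- Minimum staff: noncentral-F power was computed with effect size f = 0.20, four measures, nine sites, α = 0.05 and power 0.80. The 0.10 was read as the correlation between repeated measures, and sphericity was assumed. The noncentrality is f² × N × 4 / (1 − 0.10) for the within and interaction tests, and f² × N × 4 / (1 + 3 × 0.10) for the between test. The within test needs 63 (stated: 43). The interaction and between tests need 133 and 131, or 135 when rounded up to a multiple of nine (stated: 189).
- The value 43 appears with a correlation of 0.4. The value 189 appears with a correlation of 0.3 (between test), or with a sphericity factor of 0.6 (interaction, correlation 0.10). No single set tried gave both.
- Every variant concerns change or differences in staff measures. None involves youth, opioid initiation or cost.

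**3. What a real H3 test could detect (illustration)**

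Inputs: 120 SRP and 240 TBRI dyads, with initiation rates of 35% and 25% (Power); 3 of 9 sites already using TBRI at project start (Study samples and recruitment). Assumptions: equal site sizes, no clustering, two-sided α = 0.05, 80% power (multiplier 1.960 + 0.842 = 2.80).
- Events: 120 × 0.35 = 42 and 240 × 0.25 = 60, total 102.
- By cell: SRP 14 (3 sites) and 28 (6 sites); TBRI 20 and 40.
- Using cell events: variance of the log ratio of hazard ratios = 1/14 + 1/28 + 1/20 + 1/40 = 0.182, SE 0.43. Detectable ratio = exp(2.80 × 0.427) ≈ 3.3.
- Using total events and 1:2 allocation: 34 and 68 events, each multiplied by 1/3 × 2/3 = 2/9. SE = √(1/7.56 + 1/15.11) = 0.446. Detectable ratio = exp(2.80 × 0.446) ≈ 3.5.
- Power with the second SE: about 15% at a ratio of 1.5, 34% at 2.0 and 69% at 3.0.

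**The case against.** The strongest defence is that moderation is plainly intended. The implementation overlay section says so, and the Discussion names multilevel modelling by degree of site TBRI use, which is close to the right analysis. The intent is clear, but the Discussion offers only a possibility. The Data analysis plan fixes a different model for H3 by name, so the document is inconsistent with itself. For the same reason this is not a detail left to a statistical analysis plan.

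Time might also be meant to stand for stage, since each site is its own control. The text does not say so, and time by site would still carry no measure of facility use.

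Several stronger readings are tempting but not supported:
- **That H3 excludes opioid initiation, or that its model is really a staff-measure model.** The outcomes are simply unnamed. Change in implementation measures already has its own model in an earlier sentence, which weakens the second reading.
- **That H4 lacks an analysis.** The Data analysis plan gives it micro-costing, multilevel models and bootstrap intervals. Only its label in the Power section is wrong.
- **That 43 and 189 are miscalculated.** The documents do not say what the 0.10 correlation refers to, and they give no sphericity assumption. Failure to reproduce the figures therefore proves nothing, and this point does not depend on it.

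The illustration also has limits. Recruitment is proportional to census, so equal site sizes are a simplification. Because all facilities receive TBRI training at the start of Stage 2, use at project start may not describe use later.

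**Conclusion.** The concern holds. The model fixed for H3 cannot test H3 whatever outcome is put into it, because it has no condition, no facility-use measure and no interaction between them. It also conflicts with the stated moderation purpose. This conclusion rests on the wording alone and needs no assumption.

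The staff-based calculation supports a statement about change in staff measures, and nothing about H3 or H4.

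The detectable ratio of about 3.3 to 3.5 is illustrative. It depends on the plan's assumed event rates, equal site sizes and a two-group split of sites, and clustering by nine sites would make it worse. It is enough to show that a correct H3 test will be imprecise.

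**What to change.** - **H3 model.** Replace the H3 sentence with a youth time-to-opioid-initiation model containing condition, facility TBRI use and their interaction, with site effects and inference suited to nine sites.
- **Moderator.** Define facility use as one value per site that does not change with condition, for example the site mean TBRI Professional Use score at the start of Stage 1, which Table 5 already schedules. A score taken separately in each stage would be entangled with condition, because standard practice always precedes TBRI at a site and staff training begins with Stage 2. Use during Stage 2 can serve as a sensitivity analysis.
- **Reporting.** Give the interaction with its confidence interval and state that precision is low.
- **Power section.** Relabel the 203 against 43 and 189 calculation as power for change in staff implementation measures, and remove the reference to H3 and H4.

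The cost is revised wording and one further model on data already being collected. The real price is that H3 can be claimed only as a low-precision, effectively exploratory result.
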